## Methods

### Study design

This multi-center study examines the addition of two parental components to a TF-CBT-based treatment for children exposed to IPV, which results in a 2 (preparatory program present versus absent) x 2 (parent-child interaction present versus absent) factorial randomized experimental component trial. The study includes pre-treatment (T1), treatment, post-treatment (T2), and a 6-month follow-up (T3) assessment, and will include 100 children and their custodial parents (Fig. 1 depicts the study design). The baseline assessment (T1, see Fig. 2) will take place one week prior to the start of the 6-week preparatory program. To ensure comparability across treatment conditions, in the “No preparatory program” condition, parents and children will be assessed 7 weeks before the beginning of the TF-CBT-based treatment. Additionally, parents and children will be assessed three times during treatment, namely at the beginning of the intervention (session 1), after sharing the trauma narrative of the child with the parent (session 9), and at the end of the intervention (session 15). These measurements allow us to test mediating pathways [47], and allow us to monitor, and if necessary control for, new IPV or other stressful incidents. The second assessment (T2) will take place one week after the last session of the TF-CBT-based treatment for all four conditions. The third assessment (T3) will be at a follow-up, six months after the last session of the treatment. Regardless of condition, all participants receive the standard TF-CBT-based treatment. The difference lies in the addition of the two parental components. Families who are assigned to “No preparatory program“ or “No parent-child interaction” conditions will not receive an alternative component additionally to standard TF-CBT based treatment.

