**Fig. 2 Fig2:**
[figure not shown]
Research procedure. After informed consent is obtained for all parent-child dyads to form a group, they will all participate in the T1 assessments. Parents and children are asked to fill out questionnaires and to participate in two observational tasks. Additionally, the parent is interviewed with respect to the observational tasks. After T1, the group will be randomly assigned to one of the four treatment conditions by an independent researcher using a randomization procedure with lottery drawings. Condition 1 & 2 will start one week after T1, and condition 3 & 4 will start seven weeks after T1. One week (T2) and six months (T3) after the end of the program, parents and children are again invited to fill out questionnaires. At all assessments, the teacher is also sent a questionnaire

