### Intervention

The HORIZON [10, 44] is a 21-session TF-CBT-based group intervention for children who have been exposed to IPV. The aim of the intervention is to help children process the traumatic experiences of having been exposed to IPV. The aim of the parent group is to guide parents to helping their traumatized children in this process. Both children and parents receive a therapy book [48, 49]. This book is used weekly during the therapy sessions for information about the topic, assignments, and drawings and in between sessions for homework.

For the description of the intervention we distinguish three parts. First, the *Preparatory Program* is developed for parents and consists of six sessions. As mentioned above, it aims to increase parental availability and insightfulness in children’s needs. Parents are coached to accurately read the behavioral and emotional signals of their children’s needs, and to adequately respond to these signals.

The second part of the intervention consists the TF-CBT based core program, which comprises of parallel groups for parents and children and consists of fifteen weekly sessions. Because the HORIZON is trauma-focused and based on cognitive behavioral therapy principles, it includes similar components as TF-CBT that were described and studied by Cohen and Mannarino [17]. Specifically, it includes components such as psycho-education, relaxation, affective expression and modulation, cognitive coping and processing, trauma narrative, sharing the trauma narrative with their (non-violent) parent and parenting skills. Similar to TF-CBT these components are covered in the HORIZON by the following exercises and themes: psycho-education about therapy, violence and conflicts, and posttraumatic stress; training of emotion regulation skills; addressing incorrect attributions about conflict and violence; expressing and sharing the IPV experiences; managing anger, guilt and shame, handling nightmares; good and bad sides of mother and father; and future safety. These weekly sessions have a duration of 60 min. After each session, the therapists of both the parent and child groups will evaluate the session and share information about children’s as well as parents’ progress.

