The third part, the Parent Child Interaction Sessions (PCIS), takes place adjacent to the parallel parent and child group sessions when the parent group joins the children’s group. During 30-min sessions, parents and children are given the opportunity to interact with each other. The aim of these sessions for the parents is to learn to show more emotional supportive behavior, more involvement (e.g., talking together), more praise, less harsh discipline, and increase parental presence (e.g., time spent together). During Parent Child Interaction Sessions, parents can train and practice this parenting behavior through exercises in the presence of a therapist. Additionally, therapists observe the parent-child interaction and intervene when necessary. Therapists also give parents feedback on their parenting behavior in Parent Child Interaction Sessions during the following session in the parallel parent group. Children will receive feedback on their interaction behavior directly during the sessions together with their parents.

During the study, all children and parents in all four conditions will receive the TF-CBT based core treatment as described in part two above. There is no waiting list or control intervention.

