### Secondary objectives

To investigate associated changes between: child symptoms, on the one hand, and 1) child responses (i.e., child emotional, behavioral, and cognitive responses), 2) parental availability and 3) parent-child interaction on the other, we will use the stepwise procedure in multivariate regression analyses with a maximum of 4 tested predictors. With a sample size of 100, alpha of .05 and medium effect size (f^2^ = .15), we will achieve a power of .87 in analyses with 4 individual predictors. We will use latent variables for child responses, parental availability and parent-child interaction.

We will also use multivariate regression analyses to study the fourth goal, namely which mechanisms explain how the two components added to the TF-CBT-based Horizon treatment contribute to the effectiveness of TF-CBT-based Horizon treatment. We will follow Holmbeck’s recommendations [120] for these mediational analyses and will test the robustness of our results by using the bootstrapping method. These analyses will allow us to determine whether the parent-child interaction variables and parental availability partly or fully mediate the effects of each parental component on child symptoms. Specifically, we will test whether, as predicted, the preparatory program leads to increased parental availability and whether the parent-child interaction sessions lead to improved parenting behavior. Also, we will explore whether these changes lead to a reduction in symptoms. Because at least partial mediation is assumed, a small to medium effect size is chosen (f^2^ = .10). Two models are tested. A first model with component 1 (preparatory parent program) and parent availability as independent variables. And a second model with component 2 (parent-child interaction sessions) and parent-child interaction as independent variables. With a sample size of 100, alpha of .05 and medium effect size (f^2^ = .10), we will achieve a power of .80 if 2 predictors are tested in the regression.

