## Discussion

This study aims to bridge the gap between clinical practice and scientific research [122]. It examines mechanisms underlying change in psychotherapy for children exposed to IPV, explains how components of therapy work, and identifies moderators of treatment effects. The results, which are obtained in a RCT-study in collaboration with different trauma centers, will provide unique insights to improve clinical decision-making.

First, the RCT-design provides the best possible controls for evaluating the efficacy of psychiatric treatment. Rather than using a waiting list control group, the study zooms in on two parental components and mechanisms of change not yet investigated. All children receive TF-CBT, an established treatment for traumatized children [17], including psycho-education, parenting skills, relaxation, affective expression and modulation, trauma narrative, and cognitive coping and processing.

Second, the study focuses on the efficacy of two IPV-related parental components added to TF-CBT. To date, research on effective components of treatment for post-traumatic stress disorder focused on trauma-oriented components [123]. Research on effective components of TF-CBT focused on the trauma-narrative [124], on treatment lengths [124], and on inclusion of parents [125]. Nevertheless TF-CBT is less effective for children exposed to IPV than for children otherwise traumatized [9]. Children exposed to IPV are not only traumatized, but IPV also directly and indirectly affects their emotional, cognitive and behavioral responses. By considering this complexity this study provides important insights into the efficacy of specific IPV-related parental components. These insights are crucial to improve the treatment and maximize its effects for this specific target group [124].

The use of multiple informants (parent, child and teacher) and independent observations and interviews are likely to diminish reporting-bias. To pinpoint underlying mechanisms and assess the longer-term consequences of the intervention multiple data collections takes place, including a follow-up at 6 months after the end of treatment. This converging evidence will allow us to establish the reliability and validity of the collected information considerably.

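### The two own-target mediation models cannot separate a component-specific mechanism from the effect of extra therapist contact; each component's effect on both mediator sets should be estimated

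*Protocol article*

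**What the plan says.** **Comparator.** Study design (Protocol article) states that families without a component "will not receive an alternative component additionally to standard TF-CBT based treatment". Intervention adds: "There is no waiting list or control intervention". Primary objectives defines each factor as component present versus absent.

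**Amount of contact.** Under Intervention, the preparatory program "is developed for parents and consists of six sessions", with no session length given. The core program "consists of fifteen weekly sessions", and "These weekly sessions have a duration of 60 min". The interaction sessions last 30 minutes; the Background section on parent-child interaction calls them weekly and places them after the core sessions.

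**Timing.** The legend of Fig. 2 says: "Condition 1 & 2 will start one week after T1, and condition 3 & 4 will start seven weeks after T1".

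**Mechanism analysis.** Secondary objectives, under Statistical analyses and sample size calculation, names two models. The first is "A first model with component 1 (preparatory parent program) and parent availability as independent variables"; the second pairs the interaction sessions with parent-child interaction in the same way. The directional hypotheses there and under Trial objectives use the same pairing.

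**Intended reading.** The Discussion says the study "explains how components of therapy work". Its limitation paragraph mentions only the two-parent consent rule.

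**The concern.** Goal 4 asks more than whether an added component helps. It asks whether the preparatory program works through parental availability and the interaction sessions through parenting. Families given a component receive its content and also more therapist and group contact, and nothing balances that contact in the other arms.

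More attention and support of any kind might also raise reported availability or improve reported parenting. If so, an own-target model would come out positive whether or not the content mattered. Mediation of symptom change does not resolve this, because availability raised by general support could mediate symptoms just as well. At stake is the attribution of an effect to a specific mechanism, not the estimate of whether adding the component helps.

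**Working it through.** **1. The plan's own figures.** Noncentral F for multiple regression, noncentrality f² x N, degrees of freedom k and N - k - 1, alpha .05, N = 100, independent data:

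| Analysis | f² | k | Stated power | Recomputed |
|---|---|---|---|---|
| Primary | .15 | 5 | .84 | .843 |
| Associated change | .15 | 4 | .87 | .874 |
| Mediation | .10 | 2 | .80 | .803 |

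All three reproduce. The point does not depend on them.

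**2. Contact difference for parents.**
- Core: 15 x 60 = 900 min (15 h).
- Interaction sessions, assuming one after each core session: 15 x 30 = 450 min, and 450/900 = +50%.
- Preparatory program, assuming 30 to 90 min per session because the length is not stated: 6 x 30 = 180 to 6 x 90 = 540 min, or +20% to +60%.
- Both components: 900 + 450 + 180 = 1,530 min (25.5 h) to 900 + 450 + 540 = 1,890 min (31.5 h), which is 1.7 to 2.1 times the core.

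**3. What the own-target models can identify.** Let a component shift its own mediator by s + g, where s is due to content and g to contact. The model's component-to-mediator path estimates only the sum. With s = 0.5, g = 0 or with s = 0, g = 0.5 (arbitrary values in SD units), its expectation is 0.5. The two cases differ in the effect on the other mediator: about 0 in the first if content does not spill over, and about 0.5 in the second if contact acts alike on both mediators. Neither named model includes that off-target path. The third-goal regressions and the cross-lagged models use all mediator sets, but they relate mediators to symptoms, not to assignment. The session 6 comparison of parent and child accounts is again an own-target contrast for the preparatory program.

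**4. Precision of an on-target minus off-target difference.** Assume a balanced design with 50 children at each level of a factor, independent data, mediators scaled to SD 1 and correlation r between them.
- SE of one main effect = sqrt(1/50 + 1/50) = 0.20.
- SE of the difference = 0.20 x sqrt(2(1 - r)): 0.283 at r = 0 and 0.20 at r = 0.5.
- 95% half-width = 1.96 x SE: 0.55 and 0.39 SD.
- With an assumed on-target effect of 0.55 SD and off-target effect of half that, the difference is 0.275. Then 0.275/0.283 = 0.97 gives power of about 16%, and 0.275/0.20 = 1.375 gives about 28%.

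Allocation is by therapy group, so real intervals may be wider still.

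**The case against.** **The comparator fits the question asked.** Present versus absent is the declared contrast, and the protocol says openly that nothing replaces an absent component. This stands. The primary analysis needs no change and no attention-matched arm is called for.

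**The plan is not wholly confined to matched pairs.** The same statistical section has a sentence saying the analyses will show whether both mediator sets mediate the effect of each component. Trial objectives mentions independent and combined effects on parent and child outcomes, and Measures of mediating variables describes the tests without pairing. This stands in part. The off-target paths are not excluded, but when the section specifies its models it names two, both own-target.

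**The targets overlap.** The preparatory program also coaches parents in responding to their child. The interaction sessions also aim at parental presence and emotional support. The Security Scale, listed under parent-child variables, includes perceived availability of the parent. Off-target change can therefore come from content too. With the low power shown above, a rule requiring a significant difference would often suppress a true mechanism. This stands, and it is why the comparison should serve as evidence and not as a gate.

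**Stronger readings that the protocol does not support.**
- A reader might see a contradiction between "There is no waiting list or control intervention" and the seven-week interval after T1. The sentence follows the statement that all four conditions receive the core treatment, and the Discussion contrasts the design with a waiting-list control group. It means there is no untreated arm.
- A reader might treat the earlier start as a separate confounder. One week plus a six-week program puts the start of core treatment seven weeks after T1, the same as in the other arms. The earlier start is the preparatory program itself.
- A reader might split the primary f² of .15 equally over the two components (d = 2 x sqrt(.075) = 0.55), obtain about 77% power for a single coefficient and call it a false-positive rate. It is only the power to detect a contact effect assumed to be that large; the protocol gives no basis for that size.

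**Conclusion.** The point holds for the mechanism claim of goal 4 and not for the primary comparison. As specified, the two models can show that a component changed its own target and that the target is linked to symptoms. They cannot show that the component's particular content was responsible.

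The contact imbalance is +50% for the interaction sessions (one per core session assumed) and +20% to +60% for the preparatory program (30 to 90 minutes per session assumed). The size of any resulting misattribution is unknown, because nothing in the protocol says how strongly contact alone moves the mediators. Both mediator sets are planned for all four arms, so the factorial design already supplies evidence on specificity that the two named models leave unused.

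**What to change.** In Secondary objectives under Statistical analyses and sample size calculation:

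1. Enter both components in the mediator models and estimate the effect of each on parental availability and on parent-child interaction.
2. Put the mediators on a standardised scale. Report on-target and off-target effects, and their difference, with confidence intervals that allow for the therapy groups where the planned design-effect check calls for it.
3. State that these results are evidence on specificity and not a pass/fail condition, because the constructs overlap and the difference is estimated imprecisely.
4. There and in the Discussion, word mechanism conclusions as effects of the component including its extra contact, unless the off-target results support a more specific reading.

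The cost is a few extra regressions on measures already planned, and some rewording. No extra participants, visits or treatment are needed. The drawbacks are wide intervals for the differences and, probably, a more cautious mechanism claim.

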**Fig. 1 Fig1:**
[figure not shown]
Study Design. Random-controlled trial examining the effectiveness of two parental components

**Fig. 2 Fig2:**
[figure not shown]
Research procedure. After informed consent is obtained for all parent-child dyads to form a group, they will all participate in the T1 assessments. Parents and children are asked to fill out questionnaires and to participate in two observational tasks. Additionally, the parent is interviewed with respect to the observational tasks. After T1, the group will be randomly assigned to one of the four treatment conditions by an independent researcher using a randomization procedure with lottery drawings. Condition 1 & 2 will start one week after T1, and condition 3 & 4 will start seven weeks after T1. One week (T2) and six months (T3) after the end of the program, parents and children are again invited to fill out questionnaires. At all assessments, the teacher is also sent a questionnaire

### Randomization, blinding, and treatment allocation

Recruitment will take place in three mental health centers in The Netherlands. For each center families are referred for treatment after children have been exposed to interparental violence. As soon as a group of approximately 8 families have met the inclusion criteria for participation in the HORIZON group treatment (see Inclusion and Exclusion Criteria), and after informed consent is obtained, the families participating in the study will participate in T1 measurements. Parents and children are asked to fill out questionnaires and to participate in two observational tasks. Additionally, the parent is interviewed about the observational tasks. After T1, the group will be randomly assigned to one of the four treatment conditions (see Fig. 1) by an independent researcher using a randomization procedure with lottery drawings. Conditions 1 & 2 will start one week after T1, and conditions 3 & 4 will start seven weeks after T1. One week (T2) and six months (T3) after the end of the program, parents and children are again invited to fill out questionnaires (see Fig. 2). At all assessments the teacher is also sent a questionnaire. Typically, the intervention group consists of two child groups (4–7 years and 8–12 years, respectively) and one parent group. Usually there is only one parent group, because families often have more than one child who participate in the intervention, and because parents without visitation rights do not participate. The child groups receive treatment at the same time but in different rooms. The parents of children in both groups receive group sessions on the same time. Because it is not feasible for participating trauma centers to start four interventions at the same time, we cannot randomly assign individual children or parents to one of the four conditions. Therefore, we choose randomization by group just before the start of the group therapy and after T1. Parents and children are blind to treatment condition until randomization is carried out just before the (preparatory) program starts. Clinicians will be blind for treatment condition until all families are indicated for treatment. The assessments include videotaped observational tasks. Independent research assistants will code these videos. All coders are blind for treatment condition. Sometimes it will take a few months before families can participate in one of the four group interventions, due to waiting lists and enrollment numbers to form treatment groups. If necessary, parents and children will receive family or individual stabilization intervention during this time. Independent of their experiences with treatment preceding participation in the HORIZON, all participating families will be measured at T1 at the same time to ensure comparability of the families in the study.

### Study population

The population of this study will consist of 100 children exposed to IPV and their custodial parent who are referred by the Dutch Youth Care Agency (Bureau Jeugdzorg) or a physician for treatment of the child after exposure to IPV.

### Inclusion and exclusion criteria

Typically, children are referred to the HORIZON treatment when they meet the following criteria established during an intake-interview with a trained therapist and standardized questionnaires: 1) the child has been exposed to IPV (or violence between a parent and a cohabitant); 2) the child is no longer exposed to IPV (or violence between a parent and a cohabitant) 3) the child is between 4 and 12 years old; 4) both custodial parents gave written informed consent consistent with the Dutch legislation; 5) the child has trauma symptoms or behavioral problems; 6) the child can control his or her (sexual) impulses; 7) the child’s behavior is not dangerous to other children; 8) both child and custodial parent have sufficient cognitive and language capacities to follow a group treatment; 9) at least one custodial parent is able to participate in the parent-group.

If parents are unable to participate in the group therapy, for example, because they do not speak sufficient Dutch and have to receive individual treatment potentially with the help of a translator, parent and child will be excluded from the study. Children with severe psychopathology who represent a danger to other children receive individual treatment to stabilize their psychopathological problems. When stabilization is completed, children can participate in group therapy and will be included in the study.

